### Randomization and masking

Randomization will be controlled centrally based on a predefined randomization schedule using block randomization using an Interactive Web and Voice Response System (IWRS) system maintained by an external service provider. Randomization was stratified by for regions (Japan/non-Japan). Access to the randomization list is restricted to designated people of the service provider not involved in the conduct or analysis of the trial. The treating physician (see below) transmits data critical for the randomization procedure via the IWRS system. All patients and study personnel will be blinded. Standard measures will be taken for the placebo and IgPro20 to ensure adequate blinding. A “two-physician” approach is implemented to reduce the chance of potential study unblinding. The “treating” physician will be the primary contact for the patient and will be responsible for all patient-related questions, adverse event (AE) evaluation, and for all other study-related tasks. A second “evaluating” physician will be responsible for assessment of efficacy variables. The evaluating physician does not have access to any data collected by the treating physician. For interim analysis and ongoing risk-benefit evaluations, members of the independent data monitoring committee may need to be unblinded. Access to study documents containing information on IgG levels and treatment groups will be restricted to people not directly involved in the study.

In case of an emergency and if necessary to make an adequate treatment decision, the blind can be broken by the treating physician using the interactive voice/web response system. Patients in whom the blind code has been broken will be discontinued from the study after a completion visit.

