#### Exploratory outcomes

Nerve conduction studies will be performed in a standardized manner after appropriate warming of the extremities. An electrophysiology manual will be provided to all participating centers describing in detail all nerve-conduction-study procedures. Nerve conduction studies will be performed at baseline and at the completion visit.

Quality of life will be assessed using the EuroQoL 5-Dimension Questionnaire (EQ-5D), Treatment Satisfaction Questionnaire for Medication (TSQM), and Work Productivity and Activity Impairment Questionnaire for General Health (WPAI-GH) [35–39]. These instruments will be completed by the patients themselves at screening, baseline, SC week 9, and at the completion visit.

The EQ-5D is a simple, generic measure of health status, consisting of two components: a 0 to 100 mm visual analog scale (VAS) assessing overall health on the day of assessment and five questions covering five health dimensions [39]. The TSQM (version 1.4) is a 14-item general instrument that measures the major dimensions of satisfaction with a medication [36]. Scores on the TSQM scales range from 0 (indicating poor satisfaction) to 100 (indicating perfect satisfaction).

The WPAI-GH questionnaire was developed to measure the effect of general health and symptom severity on work productivity and regular activities [38]. A higher score on the WPAI-GH indicates greater impairment and less productivity.

Patient preference for IV or SC treatment will be assessed via a questionnaire consisting of three options: prefer current treatment [SCIg], prefer previous treatment [IVIg], and have no preference. In addition, a selection of predefined reasons for their preference will be provided. The patient preference for treatment questionnaire will be completed at SC week 9 and at the completion visit. Other exploratory outcome measures are hematology, serum chemistry, virology assessments, vital sign measurements, and physical examination.

Pharmacokinetic variables will be restricted to serum IgG levels collected at the screening visit; before the first IVIg infusions on day 1, week 1, week 4, at baseline, and at SC weeks 9 and 17; and at the completion visit. For patients who receive IVIg rescue medication, IgG levels will additionally be assessed before the first infusion of IVIg rescue medication, before the final infusion of the loading dose, and at each subsequent maintenance dose.

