### Statistical analysis

#### Sample size

The study is powered to show that the percentage of patients having a CIDP relapse or withdrawing from the study during the SC treatment will be statistically significantly higher for the placebo group than for at least one of the examined IgPro20 doses arms. A monotonic dose response is expected with placebo ≥ IgPro20 low dose ≥ IgPro20 high dose.

The percentages of patients who reach an endpoint (i.e., relapse or withdraw during SC treatment) will be assumed to be 35 % for the IgPro20 high dose, 52 % for the IgPro20 low dose, and 65 % for placebo. These numbers are based on the (recalculated) data of the ICE study extension period [32], which are adopted based on differences in the study setup. The fraction of IVIg independent patients included is assumed to be 15 %; those patients are believed to have a relapse rate of 10 % regardless of treatment.

The exact Cochran-Armitage trend test with equally spaced scores has been used for the sample-size calculation. With a one-sided significance level of 2.5 %, a sample size of 58 is needed in each treatment arm to achieve a power of 90 % in an intention-to-treat analysis based on the above assumptions. Thus, the overall sample size will be 174 patients treated either with IgPro20 or placebo. Accounting for patients who will not pass the IgG dependency test and IVIg restabilization period, up to 350 patients need to be screened to ensure that 174 patients are treated with IgPro20 or placebo.

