Electrophysiological parameters (average distal latency, average proximal latency, overall average conduction velocity, average conduction block, and average compound muscle action potential amplitude)			
		By treatment and by treatment and subgroup: - Descriptive statistics - Change from reference visit - Between-treatment comparisons of the changes from baseline: analysis of variance (ANOVA) model^d^	
IgG level			
	Overall: - Descriptive statistics - Change from reference visit	By treatment and by treatment and subgroup: - Descriptive statistics - Change from reference visit	Overall: - Descriptive statistics - Change from reference visit
EQ-5D dimensions, TSQM, WPAI-GH			
	Overall: - Descriptive statistics	By treatment: - Descriptive statistics - Change from reference visit - Comparison between treatments of changes from reference visit; exact Jonckheere-Terpstra test^a^ - Comparisons between each IgPro20 dose group and placebo group, and the comparison between the two IgPro20 dose groups of changes from reference visit; Wilcoxon rank sum test^b^	Overall: - Descriptive statistics
Patient preference for treatment questionnaire			
		By treatment: - Descriptive statistics	

*EQ-5D* EuroQoL 5-Dimension Questionnaire, *IgG* immunoglobulin G, *ITTS* intention-to-treat set, *IVIg* intravenous immunoglobulin, *MRC* Medical Research Council, *PSDS* pre-randomization safety data set, I-*RODS* Inflammatory-Rasch-built Overall Disability Scale, RSDS, rescue safety data set, *SC* subcutaneous, *TSQM* Treatment Satisfaction Questionnaire for Medication, *WPAI-GH* Work Productivity and Activity Impairment Questionnaire for General Health

^a^Exact Jonckheere-Terpstra test see ref [54]

^b^For each pair-wise comparison, the one-sided *p* value from the Wilcoxon rank sum test and the Hodges-Lehmann estimate of the median difference between treatments will be presented together with the corresponding two-sided 95 % Moses confidence interval

^c^Overall between-treatment comparison will be performed using the log-rank test for trend, all pair-wise comparisons will be performed using the log-rank test

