^d^Treatment and region (Japan, non-Japan) will be used as explanatory variables. Within the framework of this ANOVA model, comparisons of each IgPro20 dose with placebo, and the comparison of the two IgPro20 doses will be performed. For these comparisons, the least squares mean for each treatment group, an estimate of the difference between treatments (if applicable), corresponding 95 % confidence interval and 2-sided p-values will be presented

**Table 3 Tab3:** Overview of sensitivity analyses

Withdrawal reasons	Assignment of patients in:				
	Primary analysis	Sensitivity analysis			
		A	B	C	D^a^
The patient experiences a CIDP relapse during the SC treatment period (lack of efficacy)	Relapser	Relapser	Relapser	Relapser	Relapser
The investigator advises that the patient’s safety or wellbeing could be compromised by further participation in the study (physician decision)	Relapser	Non-relapsers	Relapser	Not used for analysis	Censored
The patient receives prohibited medication (protocol violation)					Censored
Other withdrawal reason (other, adverse event, death, lost to follow-up, protocol violation, study termination by sponsor, and withdrawal by patient)			Non-relapsers		Censored
Patient continues to study end	Non-relapsers	Non-relapsers	Non-relapsers	Non-relapsers	Non-relapsers

*CIPD* chronic inflammatory demyelinating polyneuropathy, *SC* subcutaneous

^a^Exploratory sensitivity analysis

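### The exploratory electrophysiology model analyses change from baseline without the baseline value as a covariate: valid, but generally less precise than ANCOVA on the same data

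*Protocol article*

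**What the plan says.** The electrophysiology row of Table 2 (Efficacy evaluation secondary outcomes) covers average distal latency, average proximal latency, overall average conduction velocity, average conduction block and average compound muscle action potential amplitude. For the SC treatment period it plans "Between-treatment comparisons of the changes from baseline: analysis of variance (ANOVA) model".

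Footnote d gives the terms of that model: "Treatment and region (Japan, non-Japan) will be used as explanatory variables". Within it, "comparisons of each IgPro20 dose with placebo, and the comparison of the two IgPro20 doses will be performed". Least-squares means and treatment differences are to be reported, and the "corresponding 95 % confidence interval and 2-sided p-values will be presented".

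The Exploratory outcomes section confirms that the baseline value will be available: "Nerve conduction studies will be performed at baseline and at the completion visit". Nothing in the article puts that value into the model. Region is the stratification factor named under Randomization and masking, which explains why it is there.

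Nerve conduction appears only among the exploratory objectives and outcomes. The other between-arm efficacy comparisons in Table 2 use rank or log-rank tests.

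**The concern.** A change score already uses the baseline, but with a coefficient fixed at 1. ANCOVA estimates that coefficient from the data. When the true within-arm slope of completion value on baseline differs from 1, the change-score analysis has two drawbacks:

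- It carries residual variance that the baseline value could have removed.
- It leaves part of any chance baseline difference between arms in the estimated treatment contrast.

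The model is adjusted for region but not for each parameter's own baseline value. Because the article names the model and its terms outright, this is a stated choice and not a detail held over to the statistical analysis plan.

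What is at stake is the width of the intervals around the nerve conduction contrasts and how the observed differences are read. The section on appropriateness of measurements says these parameters have not previously been determined during IgG withdrawal, so the estimates may well be cited. No decision rule in the trial depends on them.

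**Working it through.** **Inputs from the article.** Outcome: change from baseline. Model terms: treatment and region. One baseline and one completion measurement per parameter. Planned arm size: 58 (Sample size). The article gives no SD, no baseline-to-completion correlation and no power for these parameters, so ρ and the SD ratio below are assumptions shown over a range.

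**The plan's own figure.** No figure is stated for this ANOVA. The 58 per arm comes from the primary endpoint (exact Cochran-Armitage trend test, one-sided 2.5 %, 90 % power, event rates 65/52/35 %) and is used here only as the arm size. Recalculated, the exact test first reaches 90 % at 57 per arm (90.2 %). At 58 it gives 87.9 %, because exact power moves in steps, and the asymptotic version gives 90.9 %. The stated figure is reproduced within that discreteness.

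**Step 1: general variance comparison.** Let s0 and s1 be the within-arm SDs at baseline and completion.

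- Var(change) = s0² + s1² − 2ρ·s0·s1
- ANCOVA residual variance = s1²(1 − ρ²)
- Difference = s0² − 2ρ·s0·s1 + ρ²·s1² = (s0 − ρ·s1)² ≥ 0

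Apart from one degree of freedom, ANCOVA therefore has no larger residual variance. The gap is zero only when ρ·s1 = s0, that is, when the slope on baseline is exactly 1.

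**Step 2: equal SDs (assumption).** Then Var(change) = 2s²(1 − ρ), the ANCOVA residual variance is s²(1 − ρ²), and the ratio is (1 + ρ)/2. The interval-width ratio is its square root. The number per arm with which ANCOVA matches the planned model at 58 is 58 × (1 + ρ)/2.

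| Assumed ρ | Variance ratio | Interval width | Equivalent n per arm |
|---|---|---|---|
| 0.5 | 0.75 | 0.866 (13 % narrower) | 43.5 |
| 0.7 | 0.85 | 0.922 (8 % narrower) | 49.3 |
| 0.9 | 0.95 | 0.975 (2.5 % narrower) | 55.1 |

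A simulation of three arms of 58 with treatment and region in both models (2000 runs for each ρ, assuming 10 % of patients in one region) gave variance ratios of 0.74, 0.83 and 0.97, close to the formula.

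**Step 3: unequal SDs (assumption, s0 = 1).**

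- ρ = 0.8, s1 = 1.25: Var(change) = 1 + 1.5625 − 2 = 0.5625; ANCOVA = 1.5625 × 0.36 = 0.5625. Ratio 1.00, no gain.
- ρ = 0.7, s1 = 1.25: Var(change) = 1 + 1.5625 − 1.75 = 0.8125; ANCOVA = 1.5625 × 0.51 = 0.797. Ratio 0.98.
- ρ = 0.7, s1 = 0.8: Var(change) = 1 + 0.64 − 1.12 = 0.52; ANCOVA = 0.64 × 0.51 = 0.326. Ratio 0.63.

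The gain can thus be nil, or larger than the equal-SD table shows.

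**Step 4: chance imbalance (equal SDs).** The standard error of a baseline difference between two arms of 58 is s√(2/58) = 0.186 s, so differences up to 1.96 × 0.186 = 0.36 s are within the usual 95 % range. Given an observed baseline difference, the change-score contrast is shifted by (ρ − 1) times it. At 0.36 s the shift in absolute value is 0.18, 0.11 or 0.04 s for ρ = 0.5, 0.7 or 0.9. The standard error of the contrast itself is 0.186 s × √(2(1 − ρ)) = 0.186, 0.144 or 0.083 s, so the shift is about 1.0, 0.8 or 0.4 of it.

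**The case against.** The strongest reply is that the planned method is not wrong. Patients are randomised, so ANOVA on change is unbiased on average and has a valid type I error; no figure or passage is contradicted. This stands. A reader might infer that the planned estimates are biased or the tests invalid, and the article does not support that. The shift in Step 4 is conditional on the imbalance that happens to be observed and averages to zero over randomisation.

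The second reply is that ANCOVA is not strictly better just because ρ is below 1. This also stands. Both that statement and the (1+ρ)/2 ratio require equal SDs at the two visits; in Step 3 the gain vanishes at ρ = 0.8 with an SD ratio of 1.25. Likewise, change need not correlate negatively with baseline. Unequal SDs are plausible here: baseline follows standardised IVIg restabilisation, whereas completion mixes relapsed and stable patients. What survives is the weaker, general result that the variance gap cannot be negative.

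Third, ρ is unknown. The article describes nerve conduction studies as objective and reliable, which if anything suggests a high ρ and, under equal SDs, a small gain.

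Finally, the outcome is exploratory and nothing in the trial is decided by it. That limits the weight of the point but does not remove the gain.

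**Conclusion.** The point holds as a minor efficiency improvement to an exploratory analysis. The planned change-score ANOVA is valid but fixes the baseline coefficient at 1. It is therefore generally less precise than ANCOVA and leaves chance baseline imbalance in the observed contrast.

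The sign of the precision result rests only on the variance identity, with a common linear slope within arms. Its size rests on assumptions: roughly 2.5 % to 13 % narrower intervals for ρ from 0.9 down to 0.5 if the SDs are equal, and anything from almost nothing to more than this if they are not. The article supplies no basis for choosing within that range.

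**What to change.** Amend footnote d of Table 2 so that the model has three explanatory terms: treatment, region and the baseline value of the parameter analysed (ANCOVA). Take the least-squares means, pairwise differences, confidence intervals and p-values from that model. The treatment coefficient is the same whether the outcome is entered as change or as completion value, so the results can still be presented as changes.

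The cost is one degree of freedom and an assumed linear baseline term for each parameter. Linearity is worth a look for conduction block, whose distribution the article does not describe. No new data are needed. The change should be written down before treatment codes are released for the final analysis; Trial status places study completion still ahead.

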#### Safety evaluation

Duration of exposure, overall exposure in patient years, the total dose of IgPro10 or IgPro20 received, and the number of infusions will be summarized for the three separate study periods, using descriptive statistics. Analyses of all AEs, including deaths, serious AEs, other significant AEs, and AEs leading to withdrawal of study drug or to study discontinuation will be conducted on both a patient level and an infusion level and will be summarized for the three separate study periods, using descriptive statistics. For SC infusions, each infusion session will be counted separately. IV infusions administered over more than 1 day will be counted as separate infusions. The time to onset and duration of the most frequent AEs will be summarized using descriptive statistics. Continuous clinical laboratory parameters (hematology and serum chemistry) will be summarized for the IVIg restabilization period, by visit, using descriptive statistics. Likewise, values and changes will be summarized for the SCIg treatment (by treatment) and IVIg rescue period.

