#### SC treatment period

Three-arm randomization will be performed: one group will receive IgPro20 at 0.2 g/kg bw plus placebo to match the volume in all three groups, one group will receive IgPro20 at 0.4 g/kg bw, and one group will receive only placebo. The total dose/volume of IgPro20 will be calculated on the basis of the bw. The weekly SC infusion of IgPro20 or placebo will be performed on 1 or 2 consecutive days in two sessions using special infusion pumps. Multiple injection sites and two pumps may be used depending on the total volume to be administered. The maximum rate is 20 mL/h in week 1, and 35 mL/h for subsequent infusions. The maximum volume per injection site is 20 mL/site in week 1 and 50 mL/site for the subsequent infusions. Patients are advised to change the injection site(s) with each administration.

Patients (or their caregiver) will be trained to apply SC home therapy during the first four SC treatment sessions at the site. If needed, up to four additional trainings will be offered. Patients will also receive detailed written instructions. To ensure compliance, patients are instructed to follow the treatment instructions carefully and to contact the treating physician/study nurse to discuss any problems with SC infusion.

Patients will bring their used, partially used, and unused vials of IgPro20/placebo every visit to the site. Treatment compliance will be monitored through a drug accountability form checking the unique vial numbers used by a patient and the recorded infusion scheme. A completion visit will be performed at SC week 25 for patients who complete the SC treatment period. Patients experiencing a CIDP relapse during the SC treatment period will receive, within 1 week, IgPro10 as IVIg rescue medication (2 g/kg bw) and will undergo a completion visit before the start of the rescue medication. Patients who withdraw for any other reason will undergo the completion visit within a week of discontinuation.

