#### Safety outcomes

Patient safety will be monitored throughout the study. AEs per infusion and number and the percent of patients with AEs will be collected for IgPro20 and for IgPro10 separately. AEs, including serious AEs, will be documented at each site visit and additionally for Japan at 4 weeks after last dose. Potential hemolysis will be assessed during the phone call on day 8 of the IVIg restabilization period. Medications will be reviewed at each site visit as well as 4 weeks after the last dose in Japan.

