For the comparison of different treatments, an assessment of the patient’s preference, which will be done with a Patient Preference for Treatment Questionnaire, is important. The safety measures used in this study (AEs, vital signs, physical and neurological examinations, laboratory investigations, and viral safety) are routine procedures for clinical studies. All other efficacy and safety measurements used in the current study are also widely used and generally recognized in the medical literature as relevant in the clinical evaluation of Ig therapy.

As the study involved many centers throughout the world, special attention was given to the standardization of outcome measures. Investigator meetings with dedicated training, on-site training, and web-based trainings were all mandatory for investigators. Central eligibility checks and strict monitoring protocols were added to the standardization. All patient questionnaires were provided in the local language of the specific country and were validated for that language.

The findings of this trial will increase knowledge about the use of SCIg in the maintenance management of CIDP patients and add another treatment modality to the armamentarium of neurologists to choose from when treating these patients. The expected benefits of weekly SCIg are a reduction in systemic AEs and an increase in patient autonomy and quality of life through self-treatment. High IgG peak levels and low trough levels are avoided, and a more constant IgG level is achieved. This is expected to result in a reduced wear-off effect at the end of the dosing period.

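### AEs per infusion, counted by SC session or IV infusion day, cannot be compared between IgPro20 and IgPro10; a rate per patient-time should be added

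*Protocol article*

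**What the plan says.** Under Safety outcomes, the protocol article names two AE measures, reported for each product: "AEs per infusion and number and the percent of patients with AEs will be collected for IgPro20 and for IgPro10 separately". The Safety evaluation section says that the AE analyses "will be conducted on both a patient level and an infusion level and will be summarized for the three separate study periods", using descriptive statistics, and then defines the infusion: "For SC infusions, each infusion session will be counted separately. IV infusions administered over more than 1 day will be counted as separate infusions". The same section also summarises duration of exposure, patient-years, total dose and number of infusions.

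The SC treatment period section says that the weekly infusion "will be performed on 1 or 2 consecutive days in two sessions". Under IVIg restabilization period, IgPro10 is given as a 2 g/kg load in week 1, then 1 g/kg at weeks 4, 7 and 10 and, if needed, week 13, with no more than 200 g per dose and 100 g per infusion day. That period lasts 10 or 13 weeks; SC treatment lasts 24.

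In the Discussion, under Appropriateness of measurements, the article writes: "The expected benefits of weekly SCIg are a reduction in systemic AEs".

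**The concern.** The rule treats the two routes differently. Two SC sessions count as two infusions even on the same day, whereas an IV dose is divided only by day. A week of SC treatment therefore adds 2 to the denominator, while an IgPro10 dose meant to last three weeks may add only 1. Dividing an IV dose over more days lowers the IV rate although neither the dose nor the AEs have changed.

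The second named measure, the percentage of patients with an AE, does not settle the matter. It is not adjusted for time, and the SC period is about twice as long as the IV period.

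The article names fewer systemic AEs as an expected benefit of SCIg. Readers who look for that benefit will set the IgPro20 and IgPro10 figures next to each other, and neither named measure is suited to that use.

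**Working it through.** The article states no AE rate or infusion count, so there is no figure of its own to reproduce. The check is a direct count.

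**Inputs from the article.** Two SC sessions per week; 4 IV doses in 10 weeks or 5 in 13; at most 100 g per infusion day and 200 g per dose.

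**Assumptions.** Body weights; IV splits beyond the minimum; SC and IV exposure as scheduled; the AE rates in the examples.

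**Formula.** At equal AEs per patient-week,

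(AEs per IV infusion) / (AEs per SC infusion) = (SC units per week) / (IV units per week).

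SC units per week = 2. The minimum number of IV units for weight w (kg) is ceil(min(2w, 200)/100) + k × ceil(w/100), with k = 3 over 10 weeks and k = 4 over 13 weeks.

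**Worked case, 75 kg, 10 weeks.** The load is 75 × 2 = 150 g, hence 2 days; three 75 g doses take 1 day each; total 5 IV units. SC over the same time: 10 × 2 = 20. The ratio is 20/5 = 4.0. Over 13 weeks it is 26/6 = 4.3. The counts are the same at 80 kg.

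| Case (assumed) | IV units, 10 / 13 weeks | Ratio, 10 / 13 weeks |
|---|---|---|
| 50 kg, fewest days | 4 / 5 | 5.0 / 5.2 |
| 75 to 80 kg, fewest days | 5 / 6 | 4.0 / 4.3 |
| 110 kg, fewest days | 8 / 10 | 2.5 / 2.6 |
| Every IV dose over 2 days | 8 / 10 | 2.5 / 2.6 |
| Load over 5 days, other doses over 2 | 11 / 13 | 1.8 / 2.0 |

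**Where the gap comes from.** Counting complete doses only, SC to IV is 10/4 = 2.5 or 13/5 = 2.6; this is dosing frequency. The session/day rule multiplies that by (2 sessions per SC dose) / (IV days per IV dose). At 75 to 80 kg over 10 weeks this is 2/(5/4) = 1.6, and 2.5 × 1.6 = 4.0. Over 13 weeks it is 2/(6/5) = 1.67, and 2.6 × 1.67 = 4.3. Across the table the rule's factor runs from 2/(11/4) = 0.73 to 2/1 = 2.0.

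**Example.** With an assumed 0.25 AE per patient-week in both periods, the SC rate is 0.25/2 = 0.125 per infusion. The IV rate over 10 weeks at 75 to 80 kg is 0.25 × 10/5 = 0.50. Giving every IV dose over 2 days makes it 0.25 × 10/8 = 0.31, with the same AEs.

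**Patient-level measure.** With an assumed 0.05 AE per patient-week and Poisson counts, the share with any AE is 1 − exp(−0.05 × weeks): 39% at 10 weeks, 48% at 13 and 70% at 24. Equal burden now looks worse for SC.

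**Patient-time rate.** At equal burden the ratio is 1.0 by construction, however a dose is divided.

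**The case against.** The strongest reply is that the plan makes no such comparison. AEs are collected separately for the two products and described by period; no test or estimate contrasts IgPro20 with IgPro10, and the remark on systemic AEs is a Discussion expectation, not an objective or endpoint. This stands. A reader might infer that the plan will declare IgPro20 several times better tolerated; the article does not support that.

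A reader might also infer that the randomized safety comparison is distorted. It is not, to any material degree. The three SC arms have matched volume, two sessions a week and one session rule, so AEs per session is roughly AEs per patient-week divided by 2 in each. Between those arms the per-infusion figure already allows for earlier exit, and a patient-time rate is close to a rescaling.

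Nor do the documents support blaming the whole gap on how doses are divided. Most of it is weekly against three-weekly dosing, and dividing IV doses further narrows it.

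It is also true that the infusion is not the only unit. A patient-level analysis is planned, and the exposure summaries give the denominators for an overall time-based rate. A condensed article that states no such rate is not in error for that reason. What remains is the stated unit: it is defined explicitly, it differs by route, and its companion measure errs the other way.

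Finally, even a patient-time rate will not make IV against SC a fair contrast. The IV period comes first, is not randomized, includes the load, and only restabilized patients go on to SC. That limits what the rate can show, but it removes the part due to counting, dosing frequency and period length.

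**Conclusion.** The point holds as a limit on interpretation with a cheap remedy. AEs per infusion, as defined, should not be read across IgPro10 and IgPro20. At equal AEs per patient-week the figure is about 2 to 5 times lower for IgPro20 (1.8 to 5.2 in the cases tried). The size depends on the assumed body weight and IV splitting and on SC doses being given in two sessions. The percentage of patients with AEs leans the opposite way, so the two measures together do not answer the question either. The primary endpoint is untouched.

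**What to change.** In the Safety evaluation section, add AE rates (all, systemic, local) per patient-week or patient-year for each study period, and by arm within the SC period, using the exposure already summarised. Base any statement about AE burden with SC versus IV treatment on these rates, and say there that the contrast is sequential and not randomized. Keep the per-infusion tables, labelled as not comparable between IgPro10 and IgPro20.

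Recounting each weekly SC dose and each complete IV dose as one administration is not a substitute, because it still leaves 10/4 = 2.5-fold.

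The cost is one more column in the safety tables.
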